### Questionnaires

Patient treatment satisfaction and quality of life will be measured using the following questionnaires, validated German versions:European Organisation for Research and Treatment of Cancer Core Quality of Life Questionnaire (EORTC QLQ-C30) (Aaronson et al. 1993; Fayers and Bottomley 2002)Functional Assessment of Chronic Illness Therapy—Treatment Satisfaction—Patient Satisfaction (FACIT-TS-PS) (Peipert, et al. 2014).

The satisfaction of participating pilot partners will be assessed using the.Collaboration Health Assessment Tool (CHAT) (Centre for Social Impact and Collaboration for Impact 2017).

### Focus groups and semi-structured interviews

Insights from interviews and focus groups will contribute to process evaluation and refinement of project components. Qualitative and quantitative data will be integrated through triangulation during data analysis and interpretation. Findings from interviews and focus groups will be compared with questionnaire data, process documentation, and clinical project data to provide a comprehensive understanding of implementation processes and outcomes. Therefore, two focus groups will be held, either on-site or virtually, one with physicians and tumour board members, and another with FDNs. Each focus group is expected to include approximately 5 purposively selected participants representing the different professional groups and pilot sites and will be conducted by two researchers—one moderating, the other observing and documenting key insights. Audio recordings (with informed consent) will be pseudonymised, transcribed, and later anonymised.

A semi-structured guide will frame discussions, focusing on the management of complex oncological cases and interdisciplinary collaboration. The semi-structured interview and focus group guides are based on the project objectives and needs assessment. They comprise predominantly open-ended questions with flexible prompts, allowing participants to elaborate on their views while ensuring consistency across data collection. Key themes include expectations, patient screening and recruitment, interdisciplinary collaboration within the cross-sectoral tumour board, technical implementation, clinical pathways, support by the Flying Data Nurses, communication and training, perceived benefits and barriers, and opportunities for improvement and long-term sustainability. The guides will be piloted within the project consortium, incorporating feedback from medical staff, and the patient interview guide will be pre-tested. Qualitative data collection will follow an iterative approach, with findings from the initial focus groups informing subsequent interview guides to further explore and validate emerging themes across participant groups.

Transcripts will follow a simplified system (Dresing and Pehl 2024), enabling efficient analysis while maintaining essential content features such as emphasis and pauses.

Transcripts will be analysed using qualitative content analysis (Flick 2018; Mayring 1983). The analysis combines deductive coding (from the interview guide) and inductive development of new codes. Meaning units will be extracted, categorised, and illustrated with anchor examples. The transcripts will be double-coded to ensure quality.

Additionally, guided one-on-one interviews with patients will follow the same protocols for recording, transcription, and analysis. Five purposively selected patients (one from each pilot site, representing different tumour entities) will be interviewed to capture a range of patient perspectives. Considering the exploratory purpose of the interviews, the aim of obtaining perspectives from all pilot sites, and the available resources during the pilot phase, a purposive sample of five patients was selected. This sample is intended to provide an initial range of patient perspectives and is not expected to be representative or to achieve thematic saturation. Transcripts will be coded independently by two researchers, with disagreements resolved through discussion and, if necessary, consultation with a third researcher.

## Data analysis

### Descriptive analyses

Disease- and treatment-specific variables will be described according to age group, gender, and year. This includes therapy use, treatment-related complications, and quality of life and how it changes over the course of the study (quarterly assessed). The questionnaires are evaluated according to the respective manuals (https://www.facit.org/measures/facit-ts-ps; Fayers et al. 1995). Additional indicators of service provision and utilisation will be assessed to generate a comprehensive overview of the care structure and treatment pathways. Sequences of diagnostic and therapeutic steps and the collaboration between providers will be illustrated. To this end, frequencies, proportion values with confidence intervals, and time intervals between events will be used as descriptive tools. Where appropriate, network-based methods such as Sankey charts may be used.

Missing values will be reported in terms of their extent and distribution. No imputation or interpolation will be performed, analyses will be based on the available data. The occurrence and pattern of missing values will also be used to identify potential areas for improvement in data collection and documentation in future projects.

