## Methods

### Study design and procedure

MISSION4Sax is designed as a non-controlled, exploratory, multicentre, prospective longitudinal feasibility study. The project will be carried out in collaboration with five pilot partners over a period of 36 months. The partners consist of three hospitals (standard and specialist care, with 145, 237 and 390 inpatient beds) and two oncology practices (with around 1350–2000 patients per quarter) serving as local study sites in Eastern Saxony. Following approval by the Ethics Committee, a twelve-month pilot phase will begin, followed by a twelve-month stabilisation phase. Recruitment starts at the beginning of the pilot phase, the last patient will be enrolled nine months before the end of the project, and the final data collection will occur six months before the end of the project.

The four sub-projects (SP 1–4) are closely interlinked in terms of content (see Fig. 2). FDNs (SP 4) accompany the enrolled patients along defined patient pathways (SP 1). The patients’ medical cases are presented in the CoSITuB (SP 2) to discuss surgical options and clinical trials. All patients are included in a database (SP 3). In parallel, a training programme for medical staff and patients (SP 4) will be implemented.

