### Primary and secondary endpoints

The primary endpoint of this project is improved access to clinically indicated, guideline-concordant surgical techniques and innovative clinical trials for cancer patients in Eastern Saxony.

As a feasibility study, the project aims to assess whether the proposed care structures and processes can be implemented successfully in routine practice. It is not designed to provide confirmatory evidence of intervention effectiveness.

Secondary endpoints are described according to the individual sub-projects in Table 1.

**Table 1 Tab1:** Overview of secondary endpoints

Sub-project	Items	Variables
SP 1: Patient pathways	Clinical outcomes	Complication rate (30 and 90 days) with Clavien-Dindo-Classification Grade III+ Mortality (in hospital, 30 and 90 days) Readmission rate (30 days)
	Patient satisfaction	Perceived quality of care Treatment satisfaction at baseline and project completion Involvement in decision-making
	Interdisciplinary collaboration	Perceived quality and coordination of care processes
	Process efficiency	Average waiting and transfer times Completeness and deviations in pathway documentation Decision-making confidence
	Sample survey of the total population of oncology patients treated at one local study site	Number of patients not included in CoSITuB Diagnosis Surgical indication Mortality
	Economic efficiency	Average length of hospital stays Duplication of diagnostic procedures
SP 2: Cooperative surgical indication tumour board (CoSITuB)	Use of CoSITuB	Number and characteristics of presented cases
	Concordance	Agreement between initial and second opinion on operability and surgical approach Number of treatment modifications
	Implementation	Surgical indications and procedures (robotic / open / minimally invasive) per site Adherence to tumour board recommendations
	Timeline tracking	Time from board decision to treatment initiation and discharge summary dispatch
SP 3: Database & IT structures	Patient data	Age Sex Diagnosis (ICD-10, staging, histology) Comorbidities
	Treatment	Surgical procedures, including R0 resection (OPS-codes) Systemic therapy
	Quality of life	General health, physical, role, emotional, cognitive and social functioning (quarterly)
	Referrer satisfaction	Care pathways, CoSITuB, FDN, and the exchange/training programme
SP 4: Training & flying data nurses (FDNs)	Communication	Number and type of site visits and exchanges
	Clinical trials	Patient screening and enrolment in innovative studies

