### Further (exploratory) analyses

For exploratory analyses, categorical variables and count variables will be evaluated using the descriptive methods specified above. For metric variables, particularly time intervals, the mean, standard deviation, and range will be reported.

Based on TDS and REDCap data, relevant clinical parameters will be described, including.Surgical approach (open/minimally invasive/robotic)Hospital and Intensive Care Unit stay duration after oncological surgeryRevision surgeries (30 days) and postoperative complications with Clavien-Dindo-Classification Grade III+ (30 and 90 days)Hospital readmissions (30 days)Time from initial diagnosis to treatmentNumber of R0 resections and lymph nodes removedReferral to a university hospital or certified cancer centre (if applicable)

Patient satisfaction will be analysed using validated questionnaires. Partner satisfaction will be assessed through qualitative analysis of focus groups.

The potential to use registry platform data for further in-depth analyses will be assessed over the course of the study.

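### Trial entry and later therapy are summarised as plain proportions although follow-up runs from 3 to about 18 months by enrolment date, so the figures have no time horizon and can mislead if split by enrolment year

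*Protocol article*

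**What the plan says.** **Timeline** (Protocol article, Study design and procedure). "The project will be carried out in collaboration with five pilot partners over a period of 36 months". After ethics approval, "a twelve-month pilot phase will begin, followed by a twelve-month stabilisation phase". Enrolment opens together with the first of these two phases. On its closing date the article says that "the last patient will be enrolled nine months before the end of the project", which is project month 27. Data capture closes three months after that, at month 30. The project month in which the pilot phase begins is not given.

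**Analysis** (Descriptive analyses). "Disease- and treatment-specific variables will be described according to age group, gender, and year". The examples named are therapy use, treatment-related complications and quality of life. The tools are frequencies, proportions with confidence intervals, and time intervals between events, all on available data without imputation. The next section, Further (exploratory) analyses, adds that "categorical variables and count variables will be evaluated using the descriptive methods specified above".

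**Outcomes.** Trial access is part of the primary endpoint and appears in Table 1 under SP 4 as "Patient screening and enrolment in innovative studies", with no time window. Therapy use has none either. Complications, revision surgery, readmission and most mortality measures do have 30- or 90-day windows.

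**The concern.** Whether a patient has ever entered a trial, or ever had later surgery or systemic therapy, depends on how long that patient was watched. Here the length of observation is set by the enrolment date. A plain proportion then mixes patients seen for 3 months with patients seen for more than a year, and answers no stated question such as the risk at 3 or at 12 months.

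Two things are at stake. First, the process evaluation is meant to give preliminary estimates for a later effectiveness study, and a proportion without a time horizon is hard to plan with. Second, if patients are grouped by enrolment year, the later group is observed for less time. Trial entry could then appear to decline although access had not changed.

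**Working it through.** The article gives no event rate or follow-up figure, so there is no stated figure to reproduce. Follow-up comes from the calendar; the event rates are assumptions.

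**Step 1: follow-up.**
- Last enrolment: 36 − 9 = month 27. Data cut: 36 − 6 = month 30. Minimum follow-up: 30 − 27 = 3 months.
- If the two 12-month phases end at month 36, recruitment starts at month 12 and maximum follow-up is 30 − 12 = 18 months. With a start at month 6 it is 24.
- Start at month 12, uniform enrolment: patients enrolled in months 12–24 have 6–18 months (mean 12.0); those enrolled in months 24–27 have 3–6 months (mean 4.5). If follow-up is capped at T4 (12 months), the means are 10.5 and 4.5.

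**Step 2: proportion at constant risk.** For a constant hazard λ and follow-up uniform on (a, b), the expected proportion is 1 − [exp(−λa) − exp(−λb)] / [λ(b − a)]. Take λ = 0.02 per month (assumed).
- Year 1 (6–18): 1 − (0.8869 − 0.6977)/0.24 = 21.1%.
- Year 2 (3–6): 1 − (0.9418 − 0.8869)/0.06 = 8.6%.
- Year 1 capped at T4: half the patients have 12 months, 1 − exp(−0.24) = 21.3%; the other half have 6–12 months, 1 − (0.8869 − 0.7866)/0.12 = 16.4%. Mean 18.9%, against 8.6%.
- Start at month 6: 30.1% against 13.8%.

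**Step 3: the pooled figure, whatever *year* means.**
- Start at month 12 (3–18 months): 1 − (0.9418 − 0.6977)/0.30 = 18.6%.
- Start at month 6 (3–24 months): 1 − (0.9418 − 0.6188)/0.42 = 23.1%.

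The same hazard gives different results because the calendar differs.

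**Step 4: other assumed rates, start at month 12, by enrolment year.**

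| Assumed 12-month risk | Year 1 | Year 2 | Year 1 capped at T4 |
|---|---|---|---|
| 10% | 10.0% | 3.9% | 8.8% |
| 30% | 29.6% | 12.5% | 26.7% |
| 60% | 58.6% | 28.9% | 54.6% |

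**Step 5: where the effect is small.**
- Early therapy: let 80% ever be treated, with proportion 0.8 × [1 − exp(−t/m)] and mean delay m. Year 1 against year 2 is 80.0% and 80.0% (m = 0.5 month), 80.0% and 78.7% (1 month), 79.3% and 70.8% (2 months).
- *Year* as year of event, N = 75, 12-month risk 30%: 9.5 first events among 60 enrolled patients in months 12–24 (15.9%), then 10.1 among 75 in months 24–30 (13.5%). The count does not fall. At 60% risk the shares are 34.5% and 25.0%, still a smaller change than by enrolment year.

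**Step 6: a common 3-month window.** At λ = 0.02, 1 − exp(−0.06) = 5.8% in both enrolment years. For 12-month risks of 10%, 30% and 60% it is 2.6%, 8.5% and 20.5% in both. The artefact disappears.

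**The case against.** A reader might infer that a false fall by year is built into the plan. The text does not support that. *Year* is undefined, and the large fall needs year of enrolment (or diagnosis). The by-year sentence names therapy use, complications and quality of life, not trial entry; the later section carries over the descriptive methods without saying that the year breakdown goes with them. Of the three named examples, complications have fixed windows, quality of life is measured at fixed visits, and therapy use probably clusters soon after enrolment because patients enter at a treatment decision. These objections stand.

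A reader might also expect a spurious fall in hospital stays to be read as better efficiency. That does not follow. The economic-efficiency measures in Table 1 are average length of stay and duplicated diagnostics. The number of stays is only a collected field in Table 2, and the length of a stay does not accumulate with follow-up as a count does.

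Two further objections stand in part. Denominators and censoring are often left to an analysis plan, which is not shown, and time intervals between events are also to be reported. But the article does more than stay silent: it names plain proportions on available data for all categorical and count variables, and sets windows for some outcomes but not for these. Also, the study disclaims effectiveness and causal attribution, and with 50–100 patients accrued evenly from month 12 the late group is only 10–20 (3/15 of the total), so a by-year contrast would be imprecise. That limits the harm, but a disclaimer on causality does not give a description the time horizon it lacks.

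**Conclusion.** The concern holds in a limited form. Follow-up is unequal by design, with a minimum of 3 months. The maximum of about 18 months assumes a pilot start at month 12 (24 if month 6). For trial entry and for later surgery or systemic therapy, the stated plain proportion has no time horizon: at an assumed 2% per month, the pooled figure is 18.6% or 23.1% depending only on the start month.

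The by-year distortion is conditional. If *year* means year of enrolment and these outcomes are shown by year, 21% against 9% (19% against 9% if capped at T4) would appear at constant risk. It is small for therapy starting within about a month and much reduced under year of event. Outcomes with 30- or 90-day windows and quality of life at fixed visits are largely unaffected, although a 90-day window can be cut short for a late enrolee operated on after enrolment. All sizes rest on uniform enrolment and assumed event rates.

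**What to change.** - Report trial entry, surgery and systemic therapy as the proportion within the first 90 days after enrolment, which every surviving, retained patient can complete.
- Beyond 90 days, report cumulative incidence with death as a competing event.
- Give any counts of hospital stays or board presentations per person-month.
- Define *year*, and compare enrolment years on fixed-window figures only.

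The cost is analysis wording: dates of therapy, trial inclusion and death are already in Table 2, so no data collection is added. The downside is that the 90-day figure omits later events, and late cumulative-incidence estimates will be imprecise with 50–100 patients.

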### Further (exploratory) analyses

For exploratory analyses, categorical variables and count variables will be evaluated using the descriptive methods specified above. For metric variables, particularly time intervals, the mean, standard deviation, and range will be reported.

Based on TDS and REDCap data, relevant clinical parameters will be described, including.Surgical approach (open/minimally invasive/robotic)Hospital and Intensive Care Unit stay duration after oncological surgeryRevision surgeries (30 days) and postoperative complications with Clavien-Dindo-Classification Grade III+ (30 and 90 days)Hospital readmissions (30 days)Time from initial diagnosis to treatmentNumber of R0 resections and lymph nodes removedReferral to a university hospital or certified cancer centre (if applicable)

Patient satisfaction will be analysed using validated questionnaires. Partner satisfaction will be assessed through qualitative analysis of focus groups.

The potential to use registry platform data for further in-depth analyses will be assessed over the course of the study.

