### Participants and recruitment

The study population consists of patients with a complex visceral oncological underlying disease, presenting at one of the five external, local trial sites in East Saxony with the following inclusion criteria:Complex underlying oncological disease, i.e. the extent or type of diagnosis or therapy of the oncological disease exceeds the possibilities of the respective site and requires extended external, interdisciplinary consultation on the medical case or requires the involvement of an expert centre (NCT/UCC),A visceral tumour entity (primary, metastases, or recurrence): Colorectal (C18, C19, C20), pancreatic (C25), oesophageal (C15), gastric (C16), biliary tract and hepatic tumours (C22.0/C22.1, C23, C24), or other rare tumour entities,A minimum age of 18 years,Ability to understand the study information and provide written informed consent,Ability to read and understand the German language,Presentation at the external trial centres.

Excluded are patients who are unable to give consent or cannot sufficiently read and understand German, as well as pregnant women. A sample size of 50–100 participants is expected. As this is a pilot feasibility study, no formal sample size calculation was performed. The anticipated sample size was determined pragmatically based on the expected recruitment estimates of the participating pilot partners and on historical case numbers during project planning.

Furthermore, the physicians at the external trial sites and the FDNs will take part in surveys as part of the process evaluation of the project.

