Private or statutory health insurance
Diagnosis: carcinoma in general
Date of initial diagnosis, reason for diagnosis, diagnosis made on, diagnostic certainty, ICD-10, UICC stage, cTNM stage, lymph node involvement yes/no
Comorbidities
Start/end of diagnosis, ICD-10
Chemotherapy
Start/end of chemotherapy, type of chemotherapy (neoadjuvant/adjuvant/palliative), cycles, medication (active ingredient), dose levels in %, type of toxicity, toxicity level, date of onset of side effects, total residual tumour
Other diagnostics/ findings
Date of diagnosis, type of diagnosis, location/department, findings, ECOG performance status, date of issue of referral form (between partners), reason for referral from partner
Postoperative findings/ histology
Date of findings, pTNM stage, UICC (classification for staging), residual tumour tissue (residual tumour), pathology with findings no., number of lymph nodes (removed/affected), tumour grading (G), recurrent disease, type of metastases, date of examination for secondary metastasis, type of secondary metastasis
Therapies
Date of therapy, type of therapy (CTx, RCTx, RTx, surgery), OPS-code
Surgeries (procedure/ course)
Date of surgery, surgical procedure (laparoscopic, robotic, open), postoperative complications according to CDC (date + type), type of treatment for the complication, highest CDC grade, reoperation in case of complications (date + type)
Tumour board case presentation/ reports (internal and external)
Date of TB presentation, reason for TB presentation, presenting physician, second opinion yes/no, category (surgical, study option, case discussion), initial opinion on resectability, second opinion on resectability, agreement between initial opinion and second opinion (yes/no), CoSITuB recommendation (surgery/CTx/RTx/no therapy/other), degree of implementation of the recommendation (fully implemented/partially implemented/not implemented), duration of: decision CoSITuB and start of the intervention, duration of: decision CoSITuB and doctor's letter, duration of: start of intervention and doctor’s letter
Hospital stays
Number, location, department, reason (causal connection to carcinoma), duration (hospital stays/ intensive care stays), readmission to intensive care unit/ reason, transfer to another hospital/ reason
Death
Date of death
Participation clinical trials
Study title, date of screenings, date of inclusion
Quality of life (EORTC-QLQ-C30)

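### Time intervals are summarised only by mean, SD and range, and the interval from first diagnosis to treatment pools new with recurrent disease, so the reported figure may mislead

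*Protocol article*

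**What the plan says.** The section Further (exploratory) analyses gives one rule for continuous measures: "For metric variables, particularly time intervals, the mean, standard deviation, and range will be reported". The list of clinical parameters beneath it includes the interval from initial diagnosis to treatment. It does not say which treatment ends the interval.

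Eligibility, under Participants and recruitment, covers "A visceral tumour entity (primary, metastases, or recurrence" among its criteria, with an expected 50–100 participants. No separate time origin or stratum is given for recurrent cases.

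Table 1 (Primary and secondary endpoints) has two further timing items. SP 1 lists "Average waiting and transfer times" without start or stop events. SP 2 lists "Time from board decision to treatment initiation and discharge summary dispatch", which starts at the board decision.

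On incomplete data, Descriptive analyses says "No imputation or interpolation will be performed, analyses will be based on the available data", and that the extent and distribution of missing values will be reported. Under Study design and procedure, "the last patient will be enrolled nine months before the end of the project"; by the same section, collection closes three months later, with six months of the project left. Table 2 records "CoSITuB recommendation (surgery/CTx/RTx/no therapy/other") as a variable, so a patient may properly have no treatment start.

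**The concern.** Waiting times are bounded at zero and usually skewed to the right. Mean and SD then depend heavily on a few long values, and the range shows only the two extremes. None of the three tells the reader what a typical patient waited.

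The interval from initial diagnosis adds a second difficulty. For a patient with new disease it measures delay to treatment. For a patient with a recurrence or a metachronous metastasis it measures something else, whichever treatment ends it. Pooling the two gives a number with no clear meaning, and the chosen summaries are the ones most sensitive to the mixture.

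A smaller matter concerns time from board decision to treatment. Patients not treated by the data cut have no interval, and the available-data rule leaves them out of the average. No rule separates those still waiting from those who died first or were never meant to be treated.

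The abstract names waiting times among the outcomes to be explored. Process data and evaluation says the study should supply preliminary estimates for a later effectiveness study. Description is the product here, so a misleading summary would pass into that planning.

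**Working it through.** The protocol states no expected waiting time, recurrence share or share untreated, so there is no figure of its own to reproduce. The text can be reasoned through directly; the sizes below are illustrations under stated assumptions.

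**Step 1. The two readings of treatment, for a recurrent case**

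- Treatment of the current episode: interval = earlier treatment and disease-free time + current wait. It is inflated as a measure of delay.
- First treatment ever: an ordinary interval, but it describes care that may predate the project.

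Neither measures delay under the new care model.

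**Step 2. Size on the current-episode reading**

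Assumptions, none from the documents: wait in new disease lognormal with mean 40 and SD 25 days; lag from first diagnosis to the current episode lognormal with mean L = 365 or 730 days and SD 0.6 × L; share p recurrent.

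Pooled mean = 40 + p × L. For example, 40 + 0.05 × 365 = 58 and 40 + 0.20 × 365 = 113.

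Median in new disease: s² = ln(1 + (25/40)²) = 0.330, so the median is 40 × exp(−0.330/2) = 34 days.

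Results from 1,000,000 simulated patients (days; where two values are given, they are for L = 365 / 730):

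| Recurrent share | Mean | SD | Median | Quartiles |
|---|---|---|---|---|
| 0% | 40 | 25 | 34 | 23–50 |
| 5% | 58 / 76 | 97 / 188 | 35 | 24–54 |
| 10% | 76 / 113 | 132 / 261 | 37 | 24–59 |
| 20% | 113 / 185 | 178 / 352 | 41 | 26–82 |
| 30% | 150 / 259 | 208 / 412 | 47 | 27–222 / 27–404 |

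Simulated means agree with the formula to within about a day. In a sample of 60, a 5% share is 0.05 × 60 = 3 patients.

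The last column shows that quartiles alone do not cure the mixture. At 30% recurrent the upper quartile is itself a recurrence interval, so separate reporting is needed as well.

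**Step 3. Board decision to treatment: patients untreated at data cut**

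Minimum follow-up for the last patient enrolled is 9 − 6 = 3 months, about 91 days. Suppose waits are lognormal with true mean m and only patients treated by the cut are averaged. With cut c, the observed mean is m × Φ((ln c − μ − s²)/s) / Φ((ln c − μ)/s).

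For m = 60, SD 50, c = 91: s² = ln(1 + (50/60)²) = 0.527, s = 0.726 and μ = ln 60 − 0.264 = 3.831. The observed mean is 60 × Φ(0.210)/Φ(0.937) = 60 × 0.583/0.826 = 42.4 days, a bias of −29.4%, with 17.4% untreated.

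| True mean (SD), days | Bias if every patient has 91 days | Bias if follow-up is uniform over 91–456 days |
|---|---|---|
| 20 (12) | −0.6% | 0.0% |
| 30 (20) | −4.7% | −0.5% |
| 45 (35) | −17.8% | −2.8% |
| 60 (50) | −29.4% | −6.4% |

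The middle column is a worst case, since only the last patient enrolled has so little follow-up. With spread follow-up the bias is small and downward, opposite in direction to the effect in step 2.

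**The case against.** The best defence has four parts.

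- Only one item, in an exploratory list, starts at initial diagnosis. The interval that belongs to the intervention starts at the board decision and is untouched by recurrence history. This stands: a reader might infer that all waiting times are counted from first diagnosis, and the documents do not support that. The SP 1 waiting-time item states no origin at all.
- Inflation needs the current-episode reading of treatment, and fuller definitions may sit in a document not shown. The first half stands, so inflation is conditional. But the summary rule is a positive choice aimed at time intervals, and under the other reading the recurrent cases still do not inform delay in this project.
- Untreated patients do not vanish from the study. The extent of missing values is reported, Table 2 records the recommendation, its degree of implementation and the date of death, and adherence to board recommendations is a secondary endpoint. This largely stands. What is lacking is a statement that these counts will appear beside the interval, since a missing-value count alone does not separate the reasons.
- The outcomes are descriptive, no test or decision rests on them, and the range would expose extreme values. This bears on severity. The range reveals that an outlier exists, not how far it has moved the mean.

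The Discussion also says that a later study should use more strictly operationalised outcome measures. That acknowledges the general limitation without removing this instance of it.

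**Conclusion.** The point holds in a limited form. Mean, SD and range alone are a poor summary of skewed intervals in 50–100 patients, and the interval from initial diagnosis has no consistent meaning once recurrent or metachronous cases are pooled with new disease. The reported figure may mislead.

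The size cannot be determined from the documents. On the current-episode reading, with an assumed 40-day true mean and a lag of 1–2 years, the mean rises by less than half at a 5% share and a 1-year lag (58 against 40 days) and to more than four times at 20% and 2 years (185 against 40). On the first-treatment reading the mean need not be inflated; the interval is then simply not about this project.

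A reader might go further and conclude that the reported delays will be badly wrong. That does not follow: the recurrence share, the lag and the meaning of treatment are all unstated, and the data-cut bias in board-to-treatment time is about 0 to −6% with spread follow-up. Nor do patients with metastases at first diagnosis belong with the problem cases, since their interval from first diagnosis is an ordinary one.

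Severity is minor to moderate: the outcomes are secondary or exploratory, but waiting times are named as something the study will explore.

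**What to change.** 1. Add median and quartiles to mean, SD and range for all time intervals.
2. Start the diagnosis-to-treatment interval at diagnosis of the index episode and end it at the first treatment after that date.
3. Report recurrent or metachronous cases separately from new disease; keep synchronous metastases with new disease.
4. Beside board-to-treatment time, give the number untreated at data cut, split into no therapy recommended, died first and still waiting. A cumulative-incidence estimate with death as a competing event is optional.

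The cost is a few lines of analysis wording and slightly more tabulation. Table 2 already holds the date of initial diagnosis, a separate diagnosis date, the examination date for secondary metastasis, and therapy, board and death dates. Recurrent disease is listed there under postoperative findings, so one added field for the date of recurrence may be needed.
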